#### 14. Potential Benefits

Potential benefits to study participants are learning skills and information that may lead to decreased risk of contracting and transmitting HIV and other STIs. The benefit to society is that the investigators may develop a better understanding of which interventions are most useful for promoting safer sex among justice-involved women.

#### 15. Alternatives

N/A

#### 16. Research at External Sites

The investigative team has conducted several randomized controlled trials (RCTs and prevention and services research in criminal justice systems, including three recent or current RCTS with the NYC Department of Probation. They have established strong collaboration with the NYC New York City Department of Probation Sites: Participants will be recruited from probation sites throughout NYC. We will also recruit participants from parole and designated ATI program sites. We will particularly target sites that serve low income minority communities in NYC most heavily affected by HIV/STIs. The investigative team has collaborated with Probation on three HIV research projects since 2008. Projected Enrollment: In 2012 there were at total of 3,115 Black women at the 5 DOP sites. Given the annual pool of Black women on probation from the five study sites (N=3,115) as of January 2012 and the given estimated number of 1,250-1500 additional Black women per year who will be placed on probation during the enrollment period at the 5 sites (N=3,993), we project a total recruitment pool of 7,045 Black women on probation specifically who may be approached for screening. Of this pool, we estimate 70% (N=5,607) will agree to complete a screening interview based on our current and recently completed studies in probation of whom 35% (1,726) will meet eligibility criteria based on studies summarized earlier and enroll in the study. This number will augmented by women on parole or an ATI program. This flow of potential participants will be ample to achieve a sample size of 420 women.

Staff from Fortune Society, which is the largest probation contract provider in NYC, and also provides services to individuals on parole and other ATI programs, will be delivering both interventions for this study (see letter of support) either at their site or at one of the probation, parole or ATI program sites. Fortune Society does not have an IRB or access to an IRB. [name], our administrative contact at Fortune Society, has indicated that they will accept Columbia as the Sole IRB for review and approval of this study. The NYC Departments of Probation and Parole, and leadership personnel from designated ATI program locations, will

provide space for recruiting participants and conducting assessments at probation, parole and ATI program sites located throughout in New York City, however, they will not have any contact with human subjects for this study. New York City (NYC) Department of Probation, Parole and ATI Sites: In New York State, probation, parole or ATI are court-ordered sentences to community supervision with certain conditions. NYC operates probation and parole departments, and ATI programs, with funding and oversight by the New York State Division of Probation and Correctional Administration (DPCA). Each of the five NYC boroughs has probation, parole and ATI program reporting sites, where offenders under supervision report to probation, parole and ATI program officers with frequencies ranging from weekly to several times a year.

Social Intervention Group- Community Research Site: The Social Intervention Group (SIG) at the Columbia University School of Social Work (CUSSW) has a new community space where we conduct all assessments and intervention sessions, which is located within a 10-minute walk of our administrative offices at CUSSW. This community space was outfitted for this study and contains two gender specific assessment rooms that are equipped to conduct the Audio Computerized Assisted Structured Interviews (ACASI), a bio-specimen lab, which is equipped to process, store and ship specimens; four private offices where the face-to-face interviews and pretest and post-test HIV/STI counseling are conducted; four intervention rooms – one of which is outfitted with PCs to conduct Web based multimedia interventions. These intervention rooms can comfortably fit up to 14 people and are equipped with the audiovisual equipment, flip charts and all other materials specific to each intervention. This community space also has two office rooms with workstations to accommodate project staff while they are in between sessions and locked file cabinets to store confidential materials.

## 17. Columbia as Lead Institution

Columbia University is the lead and sole institution implementing this project. Letters of support from Fortune Society and the New York City Departments of Probation and Parole, and designated ATI program locations are attached. As Fortune Society does not have an IRB, we applied for and received IRB coverage through Columbia University. We have also secured an IIA Agreement (FWA00022811).

## 18. E-WORTH Study protocol to allow multi-level statistical analysis

The following describes additional research procedures at to accommodate a spatial multi-level analysis of the data that incorporates neighborhood aggregate data in the statistical analyses of these data. Multi-level statistical analyses will examine the association between socio-contextual variables aggregated at the Community District and United Hospital Fund Level and outcomes of sexually transmitted infections. In order to carry out the proposed research it is necessary to attach an additional variable indicating which Community District and United Hospital Fund neighborhood corresponds to each participant. The following modification describes necessary research procedures and safeguards to protect the confidentiality and privacy of all study participants during the spatial analysis process.

### ***Research procedures***

All participants with addresses will be geocoded using QGIS software on a secure computer at the research site. Once addresses are geocoded using the spatial merging options available in QGIS the geocoded addresses will be attached to another spatial shapefile that indicates corresponding community districts and United Hospital Fund Neighborhoods. The resulting shapefile will be exported into a STATA file and the column variable

indicating addresses of participants will be deleted prior to removing the file from the secure computer at the research site for statistical analysis.

### ***Variables that will be used in this analysis***

Aggregate variables that will be used in this study include the following: HIV incidence, % uninsured, unmet medical needs, alcohol use, heroin/prescription pain medication use, sociodemographic factors that include race ethnicity, poverty, homelessness, crime complaints offense data, and arrest data. Aggregate neighborhood level sexual risk variables from the publicly available Community Health Survey include, sex without a condom and number of sexual partners. All aggregate data is fully de-identified by government agencies prior to public distribution. This study will not analyze any identifiable aggregate data in this multilevel analysis.

### ***Protection of human subjects***

The proposed research will examine the effects of neighborhood contextual factors on sexually transmitted infections and other outcomes among participants in community corrections in New York City. In addition to the measures taken to protect human subjects in the approved protocol, participants who live in either community districts or United Hospital funds with cell sizes of 5 or fewer will be ‘suppressed’ or excluded from the final dataset. No addresses will be exported in the final analytic datafile. No maps will be created visualizing the data from the E-WORTH Study. Maps will be created visualizing aggregate data for contextual variables in New York City.

### ***Geographic units of analysis***

The two Aerial Units of analysis in this study are community districts and United Hospital Fund neighborhoods **Community Districts.** There are a total of 55 community districts in New York City with corresponding community boards that advise the local borough president on city budgeting of financial resources and service delivery in each of the districts. The districts are meaningful for public policy and public health in New York City. **United Hospital Fund** The United Hospital Fund districts consist of 34 neighborhoods in New York City. The United Hospital Fund is a philanthropic organization that conducts nonprofit health service delivery research in New York City. The UHF neighborhoods provide geographic boundaries for illustrating the geographic distribution of many communicable and non-communicable diseases, social risk factors, STIs, and other variables.

Table 1. Aggregate variables that will be used in this analysis

| Variable                                   | Year | Source                                                |
|--------------------------------------------|------|-------------------------------------------------------|
| Population by Neighborhood                 | 2010 | American Community Survey (Census Bureau)             |
| HIV/AIDS overall by sex and race/ethnicity | 2013 | New York City Department of Health and Mental Hygiene |
| % Uninsured                                | 2013 | Epiqueury Dashboard Community Health Survey           |
| % with unmet medical needs                 | 2013 | Epiqueury Dashboard Community Health Survey           |
| Binge drinking                             | 2013 | Epiqueury Dashboard Community Health Survey           |
| Heavy drinking                             | 2013 | Epiqueury Dashboard Community Health Survey           |
| Heroin use                                 | 2013 | Epiqueury Dashboard Community Health Survey           |
| % Black                                    | 2010 | American community survey (Census Bureau)             |
| % Hispanic                                 | 2010 | American Community Survey (Census Bureau)             |

|                               |      |                                            |
|-------------------------------|------|--------------------------------------------|
| % White                       | 2010 | American Community Survey (Census Bureau)  |
| % Asian                       | 2010 | American Community Survey (Census Bureau)  |
| % Other                       | 2010 | American Community Survey (Census Bureau)  |
| % felt unsafe in neighborhood | 2016 | American Community Survey (Census Bureau)  |
| Crime complaints              | 2016 | New York Police Department                 |
| Number of sexual partners     | 2016 | Epiquery Dashboard Community Health Survey |
| Social indicators             | 2010 | NYC open data                              |
| Rates of Crime                | 2014 |                                            |

## **Data Analyses Plan:**

The analytic approach is built upon the investigative team's prior HIV prevention randomized clinical trials, including an intention-to-treat approach, handling missing data using both complete case and multiple imputation approaches, attrition analyses to investigate non-ignorable nonresponse, and sensitivity analyses to ascertain robustness of findings against violation of model assumptions (e.g., distribution requirements, heteroscedasticity, independence). Mixed-Effects Generalized Linear Models will be used to account for the non-independence in measures due to repeated measures with the same person. These models build upon  $g(E[(Y_{ij}|\mathbf{x}_{ij}]]) = \mathbf{x}'_{ij}\boldsymbol{\beta}$  where  $Y_{ij}$  is the outcome variable of interest for the  $i$ th participant at the  $j$ th timepoint. The components of  $\boldsymbol{\beta}$  will be intervention assignment, baseline attributes for the outcome variable, and selected sociodemographic variables based on the unbalanced randomization or relevant literature. The  $g(a)$  function represents a link function that can properly model the outcome variable as a function of measurement unit or distribution. Hypothesis testing follows the form "Assignment to E-WORTH will be associated with significantly lower/higher on outcome variable  $Y$  at the 12-month follow-up or over the follow-up period compared to assignment to the control condition where 'lower' or 'higher' is chosen in the direction of reduced risk. To test the difference in the new incidence of any STI (primary outcome) at the 12-month follow up, logistic regression models will be used. To test the effects for behavioral outcomes over the entire follow-up period, mixed-effects Poisson or negative binomial regression will be used for the number of condomless acts of sex (primary outcome), mixed-effects linear regression will be used for proportion of protected acts of intercourse, and mixed-effects logistic regression models will be used for binary behavioral outcomes.

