included in MI models to handle nonignorable nonresponse. Preliminary analyses include bivariate analyses to identify unadjusted associations among variables. Variables significantly associated with outcome variables and attrition, as well as significantly different across study arms, will be included as covariates during hypothesis testing. Generalized Linear Mixed Models (GLMM) and Generalized Estimating Equations (GEE) will be used to account for the nonindependence in measures arising from: (1) “autocorrelation” due to repeated measures with the same person; and (2) “intraclass correlation [ICC]” arising from group membership. The data analytic approach for testing hypotheses with outcome specific models for primary outcomes is presented in Table 4. Analytic strategies for secondary outcomes will follow a similar approach.

Hypothesis testing will implement an intention-to-treat approach. We will employ Generalized Linear Mixed Models (GLMM) and Generalized Estimating Equations (GEE) to account for the non-independence in measures arising from: (1) "autocorrelation" due to repeated measures with the same person; and (2) "intraclass correlation [ICC]" arising from partners who are reporting on conjoint behaviors. Hypothesis testing for Aim 1 follows the form “Assignment to E-WORTH will be associated with significantly lower/higher outcome variable Y at the 12-month follow-up compared to assignment to Streamlined HIV Testing” where ‘lower’ or ‘higher’ is chosen in the direction of reduced risk. The selection of outcome models build upon  $g(Y_{ij|x_{ij}}) = x'_{ij}w$  where  $Y_{ij}$  is the outcome of interest for the  $i$ th participant at the  $j$ th time point. The multilevel nature of the data is accounted for by modeling each predictor variable’s coefficient in the vector as dependent on group membership: where the  $i$ th participant is a member of the  $g$ th group that determines the group characteristics (i.e., elements of the vector  $w$ ) used to estimate model fit parameters in vector. The components of  $w$  will be treatment assignment, baseline attribute for the outcome variable, and those variables selected during preliminary analyses noted earlier. The  $g()$  function represents a link function that can model the outcome as a function of measurement unit or distribution.

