**2.3 Power Analyses:** From ICC estimates based on the previous WORTH trial, variance inflation factors were calculated to generate effective sample sizes used in G\*Power for Aim 1. For cumulative STI incidence, we assumed a 50% reduction (on a background cumulative incidence of 20.5%) to be clinically meaningful to detect via Poisson regression; for behavioral outcomes, projected means, standard deviations, allow for effect size  $f^2$  to be calculated and used in G\*Power. Results for primary outcomes (Figure 3) indicate that 80% power is achieved for the rate-limiting outcome (i.e., cumulative STI incidence) with an effective sample size of 372 participants; translating to a sample size of 378 participants after accounting for ICC. We then increased the starting sample size to 420 to safeguard against attrition (modeled as a complete loss of 10% of data as conservative estimate since the efficacy trial of WORTH achieved a 91% retention rate at 12-month follow-up and many of those cases provided data at earlier assessment points, thus were not “fully” missing). For secondary outcomes, power analyses participants/arm indicate 80% power to detect differences for effect sizes  $f^2 = .03$  to  $.04$  (for  $\alpha = .1$  TO  $.5$ ) with sample sizes as low as 369.

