### 3.5. Randomization

Consistent with an intention-to-treat approach for data analyses, participants will only be considered enrolled in the trial when they have been randomly assigned to a study arm. We will implement urn randomization to “force” a balance (without adding bias) between study arms with respect to the number of women per arm so that half of the women will be randomized to E-WORTH and immediately receive the individual Streamlined HIV test session followed by 4 E-WORTH group sessions and half will be randomized to and immediately receive the Streamlined HIV Testing session alone. The randomization program, which has been adapted from our previous RCTs, will also feature a combination of randomization and assignments to balance the number of women per condition per site so that the number of women assigned to each condition will be distributed across probation, parole or designated ATI program and study sites. In addition, participants randomized to the intervention arm will complete the intervention individually if less than 4 participants are enrolled at a given site in 28 calendar days. Additionally, the assignment window during the Treatment as Usual condition assignment phase will open after the first participant is assigned. We will explain the randomization process to participants during informed consent. The randomization and assignment protocol will also

ensure moderators of intervention effects assigned to study arms, thus minimizing the possible introduction of bias that can occur with urn randomization or block permutation techniques.

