**WORTH Intervention Condition:** WORTH consists of one Streamlined HIV Testing session described below followed by four 1.5-hour group sessions of 3-8 women that will be delivered by a Fortune Society facilitator provider at the Fortune Society sites. The main multimedia components used in the WORTH: (1) Narrativity: Use of videos with fictional characters who resemble different life stories of Black women affected by HIV/AIDS, drug use and criminal justice. These characters provide inspirational messages, model group support and core risk reduction skills; (2) Skill acquisition using simulated video vignettes that provides instruction and demonstration of core skills (e.g., safer sex negotiation and problem-solving skills, technical condom use skills) using culturally congruent role models followed by simulated video vignettes of role play scenarios where participants are prompted to identify common pitfalls in using skills and to rehearse appropriate responses; (3) Individual interactive exercises and logs that are designed to enhance participant's recall of core knowledge and to provide a confidential space for participants to track their individual progress in reducing risky behaviors and achieving risk reduction goals, current and ideal future social networks, and the types of support for sustaining safer behaviors, and future plans; and (4) Facilitator interactive guide which acts as a road map, prompting the facilitator to move sequentially through each activity without the need to rely on notes or memory. The basic format of each E-WORTH session remains consistent following a sequence of 5 steps: (1) an opening (quote, song, poem) which will provide a brief culturally relevant point of inspiration to engage participants; (2) Check-in to review material from the previous session, (3) a discussion to raise awareness of links between IPV, drug use, criminal justice involvement and HIV risks; (4) a skills-building component relevant to the discussion; and (5) an individual computerized rating of their sexual and drug risks; (6) an individual computerized to set appropriate risk reduction goals and plan of action which they can text to themselves. (7) identification of service needs and appropriate referrals using a computerized service tool. E-WORTH more exclusively tailored to the realities of Black women on probation, parole or ATI programs, including: (1) adding recent HIV/STI statistics for Black women in NYC on probation, parole or an ATI program to raise awareness about the epidemic in their communities; (2) using only Black characters and narratives, incorporating Afro-centric messages that

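### The analysis plan leaves out the session-group correlation that the protocol promises and the sample size allows for, omits site, and lets the data shape the adjustment set

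*Supplement*

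**What the plan says.** **Delivery.** Section 3.6 gives E-WORTH as one individual testing session followed by "four 1.5-hour group sessions of 3-8 women". The control arm receives the individual session only. Section 3.5 (Randomization) lets E-WORTH women be treated individually when fewer than 4 are enrolled at a site within 28 days.

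**Allocation.** The same section says the program will "balance the number of women per condition per site".

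**Protocol analysis.** Section 2.2 commits to GLMM and GEE for repeated measures and for an intraclass correlation due to group membership. Its next paragraph gives a different source for the ICC, namely "arising from partners who are reporting on conjoint behaviors". Section 2.3 goes from an effective 372 to 378 for the ICC, then to 420 for attrition. On covariates, section 2.2 says: "Variables significantly associated with outcome variables and attrition, as well as significantly different across study arms, will be included as covariates during hypothesis testing".

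**Data Analyses Plan.** Mixed-effects models "will be used to account for the non-independence in measures due to repeated measures with the same person". New STI incidence at 12 months is tested by logistic regression. Model components are arm, baseline attributes of the outcome, and "selected sociodemographic variables based on the unbalanced randomization or relevant literature". No group term or site term is listed. Independence appears once, among the assumptions that unspecified sensitivity analyses will examine.

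**The concern.** Women who attend the same four sessions share a facilitator and one another's influence, so their outcomes may be correlated. A standard error that treats them as independent is then too small. The protocol recognised this and paid for it in sample size, but the plan that produces the primary p-value does not carry it through. An analyst is left with three accounts of the dependence: session group, partners (who are not enrolled), or the same person over time.

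Two related gaps affect the same model. A factor that is balanced by design would normally be adjusted for. An adjustment set that depends on observed imbalance or on significance tests cannot be known before the arm and outcome data are seen, so the primary estimate is not fully fixed in advance.

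**Working it through.** **Inputs.** Control incidence 20.5%, halved to 10.25%; power 80%; effective N 372, then 378, then 420; 10% attrition (all section 2.3). Allocation 1:1 (section 3.5). Group size m = 3 to 8, in E-WORTH only (section 3.6). Two-sided alpha of .05 is stated in section 13 for the interim tests and assumed here for the sample size. The ICC value is not given.

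**1. The plan's own figures.** Sample size for Poisson regression with a 50:50 binary covariate:

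N = [z(.975)·√v0 + z(.80)·√v1]² / (ln 0.5)²

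where v0 = 1/(0.25 × 0.205) = 19.51 and v1 = 2/0.205 + 2/0.1025 = 29.27. This gives N = 363.3, rounded up to 364, within 3% of 372. Two proportions with unpooled variance give 382. For attrition, 378/0.9 = 420 exactly.

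**2. Implied allowance for clustering.** 378/372 = 1.016.
- If both arms are taken as clustered, ICC = 0.016/(m−1), which is .008 at m = 3 and .002 at m = 8.
- If only E-WORTH is clustered, ICC = 2 × 0.016/(m−1), which is .016 and .005.

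**3. Effect of ignoring groups.** With equal arms and only E-WORTH clustered, the variance of the arm difference under the null is inflated by

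V = {1 + [1 + (m−1)·ICC]}/2

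and the true type I error is 2·[1 − Φ(1.96/√V)].

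At V = 1.016, √V = 1.008 and type I error is 5.2%.

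Over a range of assumed ICCs, with all 189 E-WORTH women (378/2) in groups:

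| ICC | type I, m = 3 | m = 5 | m = 8 | power at 378, m = 3 to 8 |
|---|---|---|---|---|
| .004 | 5.0% | 5.1% | 5.2% | .80 to .79 |
| .01 | 5.1% | 5.2% | 5.4% | .79 |
| .02 | 5.2% | 5.5% | 5.8% | .79 to .78 |
| .05 | 5.6% | 6.2% | 7.1% | .78 to .75 |
| .10 | 6.2% | 7.4% | 9.2% | .77 to .70 |

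Power uses correct standard errors and unpooled variances; without clustering it is .797. A simulation of the unadjusted logistic Wald test agrees: at ICC .05 it gives 5.6%, 6.4% and 6.8% for m = 3, 6 and 8.

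**4. Omitting site.** Assuming 5 equally sized, balanced sites with a between-site SD of 0.3 to 0.8 on the logit scale, the simulated type I error of the test without site is 4.9% down to 4.2%. The direction is conservative, opposite to that of the group effect.

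**5. Choice of remedy for the group effect.** A logistic random intercept placed in E-WORTH only would compare a group-conditional log-odds in that arm with a marginal log-odds in control. Setting the true risk to 20.5% in both arms and integrating over a normal group effect, the arm coefficient targets an odds ratio of 0.99 at ICC .004, 0.91 at .05 and 0.83 at .10 (ICC on the probability scale). It would show benefit where none exists. GEE and cluster-robust errors keep both arms on the marginal scale.

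**The case against.** **The effect is negligible as planned.** The only design effect in the documents is 1.016, worth about 0.2 percentage points of type I error. Individual delivery at slow-recruiting sites dilutes clustering further, and nothing in the documents supports an ICC of .05 for a laboratory-confirmed infection. This stands, and it limits the size of the point. It does not restore the missing term: the ICC is unstated, and the 372-to-378 step is given for STI incidence only.

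**Independence is covered by sensitivity analysis.** Only generically. No method is named, and a sensitivity analysis does not define the primary standard error. The protocol also refers to a Table 4 of outcome-specific models that is not visible here, so nothing is inferred from it.

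**Stronger readings that the documents do not support.** A reader might infer that:
- the analysis plan selects covariates by significance tests. That rule is the protocol's; the plan's rule is imbalance or literature, and a literature-based list could be fixed in advance;
- omitting site makes the intervals too narrow, or departs from the protocol. It makes the test slightly conservative, and the protocol's listed components do not name site either;
- covariate selection inflates type I error by a known amount. That depends on the number and strength of candidate covariates, which the documents do not give;
- the sentence about repeated measures describes the primary STI test. It describes the mixed models; the STI test is a separate logistic regression, also without a group term.

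**Conclusion.** The point holds at modest size. The Data Analyses Plan does not carry through the group correlation that section 2.2 promises and section 2.3 allows for, and section 2.2 gives two incompatible sources for that correlation. Ignoring it costs about 0.2 points of type I error at the implied design effect. It costs 0.6 to 2.1 points only if the ICC is near .05 and every E-WORTH woman is treated in a group of 3 to 8. Neither condition is established, so a reading that the primary test is badly anti-conservative is not supported.

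The site omission is a loss of precision and a mild conservatism. The covariate rules differ between the documents, but each lets the observed data influence the adjustment set; no numerical size is claimed for that. The change is worth making because it settles the primary model in advance at almost no cost.

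**What to change.** - **Primary STI outcome:** logistic regression with arm, baseline STI status and site as fixed covariates. Use GEE or cluster-robust standard errors clustered on E-WORTH session group, treating controls and individually treated women as singletons. Specify a small-sample correction: 189 women in groups of 8 to 3 form only about 24 to 63 groups. Do not use a logistic random intercept in one arm only.
- **Behavioral outcomes:** account for session group in the same way, alongside the repeated measures.
- **Covariates:** replace the significance rule in section 2.2 and the imbalance rule in the Data Analyses Plan with one list, fixed before outcome and arm data are seen.
- **ICC definition:** reconcile the two sources given in section 2.2 and state the ICC value behind 378.

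**Cost.** Wording changes, and slightly wider intervals if the group ICC is positive. Group membership must be recoverable: section 3.4 has providers record attendance at each session, but does not say that a group identifier is captured, so this needs checking.
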